##### 3.6.1.3. Home Blood Pressure Monitoring

In order to reduce the number of possible false readings (high possibility of white coat or masked hypertension), high-normal BP and hypertension cases will be instructed, trained and asked to monitor blood pressure at home. The participants will be guided on how to select an appropriate HBPM device, how to measure their own BP (preparation, position and monitoring schedule) and will be provided some practical recommendations for optimal HBPM performance (43–45).

*3.6.1.3.1. Preparation and Position*. The participant should avoid smoking, caffeine and exercise for 30 min before measurements. They should have an empty bladder, and rest quietly in a comfortable seated position with the back supported, legs uncrossed, and both feet on the floor for 5 min before taking home BP measurements. The cuff of the device should be placed directly above the elbow and pulled taut, with the arm supported on a flat surface. Avoidance of talking or using electronic devices during BP measurements will be required. The participant will be instructed not to share the device with anyone unless this is equipped to store readings for multiple people and carry out a periodic check-up of the device.

*3.6.1.3.2. Monitoring Schedule*. HBPM will be based on 2 measurements taken at least 1 min apart in the morning and evening. Morning measurements should be made before breakfast and evening measurements should be taken before going to bed.

Current guidelines recommend that the average of all these values should be used with the exception of the first day, which should be discarded for clinical decision-making. If there is a discrepancy between office BP and home BP readings, a home BP-based diagnosis should take precedence (46). HBPM reference values are as follows:

##### 3.6.1.4. Home Blood Pressure Measurement (SBP/DBP, mm Hg)

Hypertension, ≥135 and/or ≥85 (participant will be sent to clinical visit and ABPM for follow up)

#### 3.6.2. Periodontitis

The periodontal evaluation will be done every year in terms of probing pocket depth (PPD) and clinical attachment loss (CAL). Examining 6-site-per-tooth in all natural teeth—except third molars–, measuring the distance from the cemento enamel junction (CEJ) to pocket depth and the distance from the gingival margin to the CEJ will be performed. Participants will be divided into two groups: (1) participants without periodontitis and (2) those with a diagnosis of periodontitis (mild, moderate and severe) based on *Centers for Disease Control and Prevention and American Academy of Periodontology* (CDC/AAP) definition (47), suggested for epidemiological studies by Holtfreter et al. (48). According to a recent agreement among experts from Europe and USA (48) and recent epidemiologic trends, the 2012 CDC/AAP criteria become a consensus approach for epidemiological studies worldwide (49). Furthermore, the 2017 World Workshop on the Classification of Periodontal and Peri-Implant Diseases and Conditions (50), in Appendix B, recommended that *After a long-standing debate on how to provide data to inform surveillance of periodontal disease, a recent multinational effort has suggested standard reporting of periodontal epidemiology surveys. Such efforts are important to provide comparable data across populations*.

Several international research efforts have actually made use of this definition for periodontitis cases. For instance, a recent study (51) that compared CDC/AAP Case Definition and the EFP/AAP Classification concluded that use of the EFP/AAP classification (as a possible new globally accepted classification) to assess periodontitis prevalence, severity and risk factors when conducting epidemiological surveys may not be totally reliable for use in population surveys. Hence the use of CDC/AAP in these studies is deemed more appropriate. Also, a recent systematic review and meta-analysis of the association of periodontitis with hypertension determined the CDC/AAP as a confident case definition of periodontitis (3).

The implementation of this classification improved reporting quality and permitted meaningful comparisons of the prevalence of periodontal diseases across populations in epidemiological studies (48). Indeed, many recent epidemiological studies with diverse populations in different parts of the world have used this classification (52–57), as well as (58–61) and (61–63).

For the sake of the present research and based on the international consensus just discussed, periodontitis cases will be classified as follows:

No periodontitis, there is no evidence of mild, moderate, or severe periodontitis.Mild periodontitis, is the presence of at least 2 interproximal sites with *CAL* ≥ 3 mm and at least 2 interproximal sites with *PPD* ≥ 4 mm (not on the same tooth) or 1 site with *PPD* ≥ 5 mm.Moderate periodontitis, defined as at least 2 interproximal sites with *CAL* ≥ 4 mm (not on the same tooth) or at least 2 interproximal sites with *PPD* ≥ 5 mm (not on the same tooth).Severe periodontitis, defined as having at least 2 interproximal sites with *CAL* ≥ 6 mm (not on the same tooth) and at least 1 interproximal site with *PPD* ≥ 5 mm.

### 3.7. Self Perception

Variables that represent the oral health status and their relation to oral quality of life will be included as follows:

#### 3.7.1. Oral Health Related Quality of Life

The evaluation on Oral Health-Related Quality of Life (OHRQoL) will be carried out with the abridged version of the *Oral Health Impact Profile (OHIP-14)* that has been validated in the Mexican population (64, 65). The interview will be carried out before clinical examination. It consists of 14 questions in order to evaluate the impact of oral health conditions on people's physical, mental and social well-being. Each question has five possible answers ordered from least to most frequent (0. Never, 1. Almost never, 2. Sometimes, 3. Frequently, 4. Almost always). The instrument is scored by adding the code of each response, offering a scale from 0 to 56, where the highest score represents the greatest negative impact on quality of life.

#### 3.7.2. Diet Changes Due to Chewing Problems

Participants will be questioned as follows: *Is there any type of food that you have avoided due to problems with your teeth, dentures, or mouth in the last month?* The answer to this question will be dichotomous (Yes/No), if the answer is yes, the participants will be asked what foods they have avoided.

#### 3.7.3. Self-Perception of Need for Dental Treatment

The need for dental treatment will be assessed with the question *Do you consider that you need dental treatment?* With possible answers: No = 0, Yes = 1, Maybe = 2.

#### 3.7.4. Xerostomia

Xerostomia or dry mouth feeling will be evaluated using the *Xerostomia Inventory* that has been translated and validated into Spanish (66). The Xerostomia Inventory consists of 11 questions with five possible answers (1. Never, 2. Hardly, 3. Occasionally, 4. Sometimes, 5. Very frequently), the code of each answer is added to offer a score that goes from one to 55, where the highest score suggests the greatest severity of symptoms. Participants will be asked to select one of five possible responses for the 11 questions (see note 2 in the Supplementary Material).

### 3.8. The Functionality of a Removable Prosthesis

The functionality of a removable prosthesis, retention, stability, adaptation, and integrity of the metallic structure (in case it is present), adaptation and integrity of the acrylic base will be evaluated by following *Ettinger's criteria* (see note 3 in the Supplementary Material) (67). The presence of retainers on root surfaces will be indicated. The information will be obtained by observation from the examiner.

### 3.9. Oral Hygiene

#### 3.9.1. Sampling of Biofilm (Dental Plaque) and Calculus

The biofilm and dental calculus will be obtained from the buccal and lingual surfaces of all natural teeth present according to the criteria of *Green and Vermillion* (based on the fraction of surface free of plaque) (68). For biofilm and calculus, the percent of tooth surfaces not covered, covering up to 1/3 of the surface, between 1/3-2/3 of the surface, and >2/3 covered will be calculated (see note 4 in the Supplementary Material).

#### 3.9.2. Root Remains

To assess the consequences of untreated coronal caries the *Pulp, Ulcer, Fistula, Abscess (PUFA) Index* will be used to identify if the lesion involves the pulp, if there is the presence of ulcerations, fistulas, or dental abscesses (69). The evaluation is carried out visually without the aid of any type of instrument. A single value is assigned to each tooth (see note 5 in the Supplementary Material).

#### 3.9.3. Coronal Caries

The *DMFT index (decayed, missing, and filled teeth)* will be used to evaluate dental caries experience based on the World Health Organization caries diagnostic criteria (see note 6 in the Supplementary Material) (70).

#### 3.9.4. Number of Teeth Present

A tooth is considered to be present in the mouth when any part of its crown is visible or can be touched with the tip of the probe without displacing the soft tissue or has more than one-third of the three axial surfaces of the crown.

#### 3.9.5. Gingival Bleeding

Gingival bleeding will be measured with the *Bleeding On Marginal Probing Index (BOMP)* defined by Van der Weijden et al. (71). BOMP will be recorded after inserting a PCP UNC15 periodontal probe (WHO-Hu Friedy^®^) along the marginal gingiva (~2 mm) and held at an angle of ~60° to the longitudinal axis of the tooth according to the Angulated bleeding index (AngBI); bleeding will be scored within 30 s after probing (71).

The clinical parameters will be assessed at six sites per tooth: distobuccal, buccal, mesiobuccal, distolingual, lingual and mesiolingual. Gingival units that bleed on probing will be recorded as follows: giving non-bleeding sites a score = 0, bleeding at one point a score = 1, excessive bleeding a score = 2. This index has been used in several studies and provides specific information for every gingival unit as reported in the update by the group of Van der Weijden (72). A participant will be considered to have gingival bleeding when at least one gingival margin is rated one or higher.

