#### 3.4.2. Exclusion Criteria

People diagnosed with cancer with an effect on survival.Pregnancy or lactation.People with cognitive and mental disabilities.Edentulous people.People with dental implants.People who are undergoing systematic and regular periodontal treatment.People with forms of refractory or progressive periodontal rupture, periodontitis in a rapid rate of progression, necrotizing periodontal diseases or periodontal abscess that require regular taking of antibiotics.

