### 3.5. Variables (Identification, Definition, and Measurement Scales)

#### 3.5.1. Definition of Variables

Dependent-variable of interest: Incidence of hypertension.Independent-variables of interest: Periodontal-related parameters and oral-related microbial profiles.Oral health covariates: Oral health related quality of life; diet changes; perception of need for dental treatment; xerostomia; use and functionality of removable dental prostheses; oral hygiene (presence of biofilm and dental calculus); number of natural teeth present; dental caries; root debris and gingival bleeding.

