## 6. Standardization

Three examiners will be standardized. Intra-and inter-examiner reliability of 90% will be achieved for plaque, bleeding, coronal caries and root remains measurements and 70% for periodontal measurements. Examiners will also be trained to take the subgingival dental plaque and saliva samples for oral microbiome analysis.

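### The one-site rule for gingival bleeding gives a yes/no label with little contrast if site bleeding is common, and at low site rates the label depends partly on tooth count; the percentage of bleeding sites would serve better

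*Protocol article*

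**What the plan says.** Section 3.9.5 of the protocol article sets the number of sites: "The clinical parameters will be assessed at six sites per tooth: distobuccal, buccal, mesiobuccal, distolingual, lingual and mesiolingual". Each site is graded, "giving non-bleeding sites a score = 0, bleeding at one point a score = 1, excessive bleeding a score = 2". The person-level definition follows: "A participant will be considered to have gingival bleeding when at least one gingival margin is rated one or higher". No percentage-of-sites threshold is given.

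Section 3.9.5 does not name the set of teeth. Section 3.6.2 makes the periodontal examination "in all natural teeth—except third molars". Section 3.4.2 sets no minimum number of teeth beyond excluding "Edentulous people".

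The variable's role is that of an oral health covariate: section 3.5.1 lists "number of natural teeth present; dental caries; root debris and gingival bleeding". Section 9.1.2 plans the incidence, over 30-month periods, and the relative risk of each oral variable in the study.

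**The concern.** A rule that needs one positive among many sites has a low bar, and the bar gets lower as more sites are probed. Three things follow.

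- **Contrast.** If bleeding at a site is more than rare, most participants are positive. A nearly constant covariate adjusts for little.
- **Baseline negatives.** Incidence can only be counted in people who start negative. The more people the rule calls positive at baseline, the smaller that group.
- **Lost extent.** Someone with one bleeding site and someone with a hundred receive the same label, although the difference has been recorded.

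A further effect is that, at the same site rate, a person with fewer teeth has fewer chances to be called positive. Section 1 notes that periodontitis often leads to tooth loss, so the effect runs against the disease gradient.

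**Working it through.** The documents state no site bleeding rate, expected prevalence or within-mouth correlation, so there is no figure of the plan's own to reproduce. The ranges for these quantities below are assumptions.

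**Inputs from the protocol article**
- Six sites per tooth, positive at one site scored 1 or higher (section 3.9.5).
- At most 28 teeth, carrying the exclusion of third molars over from section 3.6.2. Sites: 28 × 6 = 168.

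**Assumed inputs**
- Site bleeding rate p from 1% to 20%.
- Within-mouth correlation ρ of 0 (independent sites), 0.05, 0.1 or 0.2.
- 28, 20 or 14 teeth.

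**Step 1: independent sites.** P(positive) = 1 − (1 − p)^m, where m = 6 × teeth.
- p = 1%, m = 168: 1 − 0.99^168 = 81.5%.
- p = 2%, m = 168: 1 − 0.98^168 = 96.6%.
- p = 5%, m = 168: 1 − 0.95^168 = 99.98%.
- 90% positive is reached at p = 1 − 0.1^(1/168), about 1.4%.

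**Step 2: correlated sites.** Beta-binomial model with a = p(1/ρ − 1) and b = (1 − p)(1/ρ − 1). P(positive) = 1 − B(a, b + m)/B(a, b). With 28 teeth:

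| p | ρ = 0 | ρ = 0.05 | ρ = 0.1 | ρ = 0.2 |
|---|---|---|---|---|
| 1% | 81.5% | 35.6% | 23.9% | 14.4% |
| 2% | 96.6% | 58.6% | 42.2% | 26.8% |
| 5% | 99.98% | 89.1% | 74.7% | 54.3% |
| 10% | about 100% | 98.9% | 93.8% | 79.4% |
| 20% | about 100% | about 100% | 99.7% | 96.0% |

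Correlation moves the point of near-saturation from about 2% to roughly 10–20%. It does not abolish it, but at 1% and 2% the ceiling is gone.

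**Step 3: tooth count at the same site rate**

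| Setting | 28 teeth | 20 teeth | 14 teeth |
|---|---|---|---|
| p = 1%, ρ = 0 | 81.5% | 70.1% | 57.0% |
| p = 5%, ρ = 0 | 99.98% | 99.8% | 98.7% |
| p = 5%, ρ = 0.1 | 74.7% | 70.9% | 66.2% |

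For comparison, with 28 teeth and ρ = 0.1, moving p from 2% to 10% moves positivity from 42.2% to 93.8%.

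**Step 4: people left for incidence.** If all 1,212 planned participants (section 3.3.1) were examined at baseline and had 28 teeth:
- p = 5%, ρ = 0.1: 1,212 × (1 − 0.747) = about 307 negative.
- p = 10%, ρ = 0.1: 1,212 × (1 − 0.938) = about 75 negative.

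**Step 5: a percentage measure.** The share of bleeding sites has expectation p whatever the number of teeth. As an illustration only, take a cut-off of 10% of sites, with ρ = 0.1:
- p = 10%: 38.8% positive with 28 teeth and 36.7% with 20, against 93.8% and 91.7% under the one-site rule.
- p = 5%: 17.1% and 16.0%, against 74.7% and 70.9%.

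**The case against.** The strongest reply is that this is a minor variable whose raw data survive. Bleeding is neither exposure nor outcome. It is absent from the adjustment set of the main hypothesis (section 2.3), the specific goals (section 2.2) and the sample size (section 3.3). Periodontitis is defined by attachment loss and pocket depth (section 3.6.2). The graded site scores are kept, the number of natural teeth is a separate covariate, and section 9.1.1 lists count and gamma models, so non-binary variables are foreseen. How a covariate enters a model may properly be left to an analysis plan that is not shown. All of this stands and limits the impact. It does not remove the point, because the person-level case definition is itself printed in the article and section 9.1.2 reaches it through the incidence of each oral variable.

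Stronger readings that a reader might infer are not supported:

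- *Nearly everyone will be positive, so incidence cannot be estimated.* This needs a site rate that the documents do not give. It fails at low rates or with strong clustering, and independence between sites of one mouth is the least plausible case.
- *The label mainly reflects the number of teeth.* Where almost everyone is positive, tooth count hardly matters. Where it matters most, not everyone is positive. With correlation, a person's own bleeding level matters far more.
- *The reliability target implies many false positives.* Section 6 says "Intra-and inter-examiner reliability of 90% will be achieved for plaque, bleeding, coronal caries and root remains measurements" but names neither the statistic nor the level (site or participant). It cannot be read as a site error rate.

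**Conclusion.** The point holds in conditional form. The one-site rule is a poor person-level summary of up to 168 graded scores. At 28 teeth, near-saturation begins at a site rate of about 2% if sites are independent, and at about 10% to 20% with within-mouth correlation of 0.1 to 0.2. Dependence on tooth count is real but partial: about 11 percentage points between 28 and 20 teeth at a 1% rate with independent sites (81.5 − 70.1), and about 4 points at 5% with correlation 0.1 (74.7 − 70.9). The loss of extent needs no assumption about the site rate.

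The site rates, correlations and tooth counts are assumed, and the 168 sites rest on applying the periodontal tooth set to bleeding. The consequence falls on a secondary covariate and on its own incidence and relative-risk analyses. The main periodontitis-hypertension estimate is not directly affected.

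**What to change.** In section 3.9.5, replace the one-margin rule with the percentage of probed sites scored 1 or higher: bleeding sites divided by sites probed. Use it as a continuous covariate, and for section 9.1.2 define worsening as a change in that percentage. If a yes/no version is wanted, fix a percentage-of-sites cut-off before the data are examined; the 10% used above only illustrates the arithmetic and is not a recommended value.

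The cost is one sentence and one derived variable. The site scores are already recorded, so no new examination is needed. The only downside is that the one-site prevalence is no longer the main figure, though it can still be reported.

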## 4. Data Collection

Participants in the umbrella cohort who meet the inclusion criteria will be invited to participate in this study. The purpose of the study will be explained to them and they will be asked to sign an additional informed consent document. An appointment will be scheduled to carry out the oral health interview, dental clinical examination and sampling for the saliva and subgingival microbiota analysis at the facilities of the Graduate Studies and Research Division of SD-UNAM. The clinical examination will be performed with the person sitting in the dental chair under artificial light. It will be explained to them that strict infection control measures will be used and that all instruments will be sterile and for their exclusive use. In the event that something unusual is observed during the dental examination, the participant will be informed that it is necessary for a dentist to examine it in more detail and will be referred to the SD-UNAM clinics. To record the data an encoder will fill-in the information in the corresponding format.

The full study will be organized in five exploration stages mentioned below: 1) reception of participants, 2) collection of biological samples, 3) interviews and anthropometric measurements, 4) oral examination and 5) sample processing (see Figure 2).

**Figure 2 F2:**
[figure not shown]
Flow chart of study. The figure represents an interview sequence, sampling procedures and data management that will be carried out in the protocol. The image generated by the authors was created with the *BioRender* App.

## 5. Oral Health Diagnosis

Participants will be evaluated every year using standardized and valid clinical measurements to identify the presence of periodontitis (see Figure 1). All participants will receive detailed information about their oral health following each evaluation and will be referred to specialized periodontal treatment whenever needed, particularly if they have severe disease. Receiving periodontal treatment, however, will depend only on each participants' decision. It should be noted that our research group will not carry out any clinical intervention or pharmacological prescription. This statement is mentioned in the informed consent for the present study.

Those participants who have started phase I periodontal therapy (scaling and root planing) and have not given it continuity (at least a couple of maintenance visits every 3 months) during the follow-up (between one evaluation and another carried out by our group) *will continue to be included in the study*. End of follow-up will be given to those participants who undergo systematic and regular periodontal treatment (at intervals of 2, 3, or 4 weeks for more than 3 months) or with forms of refractory or progressive periodontal rupture, periodontitis in a rapid rate of progression, necrotizing periodontal diseases or periodontal abscess that require regular taking of antibiotics (73–75) (see Figure 1).

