#### 3.2.1. Participants and Recruitment

The study population is a sub-cohort of the participants in a cohort from the Mexico City metropolitan area (35). It is a prospective longitudinal study in which clinically healthy residents of Mexico City, between 20 and 50 years old are recruited to be evaluated every 2 years for a period of 10 years or until they develop hypertension. Anthropometric (weight, height and waist circumference), clinical and biochemical parameters (blood and urine laboratory tests with markers such as glucose, cholesterol, triglycerides, sodium and potassium, etc.), nutritional and lifestyle habits (physical activity, sleep quality, alcohol and tobacco consumption) and social determinants of health are assessed (Supplementary Material). All participants are measured periodically (every 2 years) by a battery of specific serum biomarkers of systemic inflammation. Participants will be contacted every 6 months via email or by telephone to assess their medical and dental history including treatment for hypertension and/or periodontitis, as well as any medication (including antibiotic treatment) used over the previous months (see Figure 1).

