### 5.1. Methods Collection

Sampling of saliva and subgingival plaque will be performed at baseline and at the end of follow-up in the participants selected for the oral microbiome analysis. All participants will be asked to stop taking antibiotics 3 months before and to stop mouthwashes—1 week before the clinical examination. History of occasional antibiotic consumption (outside sampling dates) will be recorded and analyzed. They will also be asked to stop tooth brushing 24 h before the clinical exam. They will be asked to refrain from eating, drinking anything other than water and chewing gum for 12 h prior to taking samples (76).

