#### 9.1.2. Longitudinal Analysis

As part of the longitudinal analysis the incidence of each oral variable included in the study in 30-month periods will be evaluated. Similarly the relative risk for each oral variable included will be evaluated according to different variables considered as risk factors (alcoholism, smoking, among others) through bivariate and multivariable analyses, using generalized linear models, logistic regression models, and multinomial regression models.

Starting with the third evaluation (baseline evaluation + first follow-up + second follow-up), trajectories of oral health conditions will be identified. From these variables associated with each one will be identified (gender, marital status, occupational class, age, education, among others). In the same way trajectories will be considered as risk factors for the development of hypertension in the study participants and will be included in neural network models.

For the statistical association analysis, participants will be classified in two groups: Group 1: without periodontitis and Group 2: with periodontitis (including all those participants that according to the CDC/AAP have mild, moderate, or severe periodontitis). For the sake of this association analysis and by following the consensus of the literature (73–75), participants in Group 2 who start periodontal treatment but do not continue with it until remission will be kept in this group and considered with periodontitis. However, a note will be made with details on the type, the extent of their treatment and the effects on their periodontal health, derived from their periodical periodontal evaluation.

This information will be used for a further *a posteriori* analysis. The information about the extent of their periodontal disease (mild, moderate and severe) will be also considered a posteriori. It is worth noticing that *a posteriori cluster analysis*, for instance, Propensity Score evaluation (93, 94) is not unusual in prospective observational studies subject to constraints, as is this case (95–99).

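### Microbiome sampling has no condition on recent scaling or root planing, so periodontitis samples, mainly at follow-up, can mix treated with untreated mouths

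*Protocol article*

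**What the plan says.** Microbiome sampling times are set in Section 5.1: "Sampling of saliva and subgingival plaque will be performed at baseline and at the end of follow-up in the participants selected". The same section lists what participants must do beforehand. They are asked "to stop taking antibiotics 3 months before and to stop mouthwashes" (the latter for 1 week), not to brush for 24 hours, and to avoid food, gum and drinks other than water for 12 hours. Professional cleaning, scaling and root planing are not on the list. Section 5.1.2 then takes the subgingival sample by curette from the root surface.

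Three further rules decide whose mouth is sampled and under which label:

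- **Entry.** Section 3.4.2 excludes "People who are undergoing systematic and regular periodontal treatment". A single recent scaling is not covered.
- **Retention.** Section 5 says of "Those participants who have started phase I periodontal therapy (scaling and root planing) and have not given it continuity" that they "will continue to be included in the study". Follow-up ends for regular treatment at intervals of 2 to 4 weeks for more than 3 months, or for disease forms that need regular antibiotics.
- **Label.** Section 9.1.2 says that Group 2 participants "who start periodontal treatment but do not continue with it until remission will be kept in this group and considered with periodontitis".

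Treatment is recorded. Under Section 3.2.1, participants are contacted every 6 months "to assess their medical and dental history including treatment for hypertension and/or periodontitis", and Section 9.1.2 notes the type, extent and effect of treatment for a posteriori analysis.

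**The concern.** Scaling and root planing disturb the same root-surface biofilm that the curette collects. A sampling rule that controls tooth brushing for 24 hours but is silent on root planing leaves the larger disturbance uncontrolled.

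The study also makes treatment more likely. Participants are told their findings after each yearly examination and referred where needed, with emphasis on severe disease (Section 5). Periodontal therapy prompted this way falls on the periodontitis group. If some of those participants are sampled after scaling and still counted as cases, the periodontitis profile at follow-up is expected to move towards the non-periodontitis profile. The change from baseline in cases would then combine natural course with the effect of treatment. The contrast rests on only 100 people per group (Section 3.3.2), so there is little room for dilution.

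**Working it through.** **1. The rules side by side**

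| Stage | Rule | Can a recently scaled mouth be sampled? |
|---|---|---|
| Baseline | 3.4.2 bars ongoing regular treatment only; 5.1 has no scaling condition | Yes, after one-off scaling |
| Follow-up, therapy started but not continued | 5 retains; 9.1.2 keeps in Group 2; 5.1 has no scaling condition | Yes, labelled periodontitis |
| Follow-up, regular treatment maintained | 3.4.3 eliminates; 5 ends follow-up | Not clearly; see the objection |

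The retention rule in Section 5 concerns treatment between study evaluations, so it can affect only the second sample. Baseline samples are exposed only through the narrow exclusion in Section 3.4.2.

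**2. The plan's own figure**

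Section 3.3.2 gives 400 samples per evaluation time: (100 + 100) people × 2 sample types = 400, which reproduces. The 100 per group is a lower bound taken from a cited network-inference method. It comes with no effect size, standard deviation or power, so the power of the microbiome contrast cannot be recomputed.

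**3. Illustration of dilution**

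Input from the plan: 100 per group. Assumed: one standardised feature compared between the groups, two-sided 0.05, nominal power 80%, a share q of cases treated before the sample, and a share r of the contrast surviving in treated cases. The documents give neither q nor r.

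- Standard error = √(2/100) = 0.1414.
- Difference detectable with 80% power = (1.960 + 0.842) × 0.1414 = 0.396.
- Share of the contrast left, k = 1 − q(1 − r).
- Power = Φ(2.802k − 1.960), since 0.396/0.1414 = 2.802 before rounding.
- Number per group to restore 80% power ≈ 100/k², rounded up.

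| q | r | k | Power | n per group to restore 80% |
|---|---|---|---|---|
| 10% | 0.5 | 0.95 | Φ(0.702) = 76% | 111 |
| 20% | 0.5 | 0.90 | Φ(0.561) = 71% | 124 |
| 10% | 0 | 0.90 | Φ(0.561) = 71% | 124 |
| 20% | 0 | 0.80 | Φ(0.281) = 61% | 157 |
| 30% | 0 | 0.70 | Φ(0.001) = 50% | 205 |

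Allowing for the extra variance that mixing creates changes these powers by less than one percentage point (for example 61.1% becomes 60.5% at q = 20%, r = 0).

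**The case against.** The strongest reply is that the main microbiome contrasts use baseline samples. Section 2.2 ties the profile-by-periodontitis comparison to baseline, and relates 60-month hypertension incidence to the baseline microbiome and baseline periodontitis. This stands. A reader might infer that the primary endpoint and Hypotheses 2 and 3 are diluted throughout, and the documents do not support that. The retention rule leaves the baseline sample alone, and the protocol gives no frequency of recent scaling at entry. For Hypothesis 3 the comparison is between people who do and do not develop hypertension. Treated cases can fall on either side, so no dilution follows from the argument above. What remains is the second sample, the change from baseline, and a smaller exposure at baseline.

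A reader might also take sampling at the end of follow-up to include people whose follow-up ended because of regular periodontal treatment. Section 3.3.2 fixes the times at baseline and 60 months, Section 3.4.3 eliminates these people, and no closing sample is described for them. That reading should not be relied on.

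It is tempting to assume that every scaled case now looks like a non-case. Section 9.1.2 retains people who did not reach remission, so partial survival of the contrast fits the text better. Referral favours severe disease, so treated cases may also have started further from the non-periodontitis profile.

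Two further points are fair, but they do not remove the concern. The pre-selection questionnaire in Section 3.4 covers dental care, but states no scaling cut-off. The treatment record supports later analysis, but it cannot restore a sample taken just after scaling. Nor is this a detail that the article merely left out: Section 5.1 gives an explicit list of conditions, and Sections 5 and 9.1.2 give explicit retention and labelling rules.

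**Conclusion.** The point holds in limited form. Followed as written, the plan allows recently scaled mouths to be sampled, and at follow-up it counts partly treated participants as periodontitis. The likely effect is dilution of the periodontitis contrast, mainly in the end-of-follow-up samples, and a change from baseline that is hard to interpret in cases.

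The size is unknown. With 10–20% of cases treated and half the contrast surviving, a nominal 80% power becomes about 76–71%. With full loss of the contrast and the same shares treated it becomes 71–61%. Both shares, the nominal power and the single-feature comparison are assumptions; none comes from the documents. This is a worthwhile, inexpensive improvement and does not invalidate the baseline comparisons.

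**What to change.** 1. In Section 5.1, add scaling, root planing and professional cleaning to the pre-sampling conditions, with a fixed window, for example the 3 months already used for antibiotics. Meet it by moving the sampling date and never the treatment.
2. Record the time since last scaling with every saliva and subgingival sample, at baseline and at follow-up.
3. Keep the all-samples follow-up contrast as planned. Prespecify a sensitivity analysis that separates, or adjusts for, participants scaled since baseline, using the treatment data already collected under Sections 3.2.1 and 9.1.2.

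Making the never-treated participants the main follow-up analysis is not recommended. It would select on care-seeking after baseline, tend to remove severe cases, and take the periodontitis group below the roughly 100 that Section 3.3.2 requires.

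The cost is one question at booking, some rebooked sampling visits and one additional analysis.
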